### Data Management and Supervision

We will assign a specific investigation team to assess outcomes and process the data, and train the team in this regard. In addition, we will formulate some basic rules for the process of patient follow-up; outcomes assessment; and data entry, coding, and storage, namely double assessment, dual entry, and checks by independent investigators. Outcome assessors will be blinded to the patients’ intervention allocation. Our institute’s scientific research supervising team, which excludes all investigators in this study, will monitor the study process, data safety and authenticity, and occurrence of adverse events.

### Statistical Analysis

Statistical analysis will be performed using SPSS for Windows (version 20; IBM Corp). The Lilliefors test will be used to examine whether the data are normally distributed. Data will be presented as percentages, mean (SD), or median (range) accordingly. The 1-tailed unpaired Student *t* test and Pearson *χ*^2^ test (or the Fisher exact test) will be used to make comparisons between different groups. The OS and progress-free survival curves will be plotted using the Kaplan-Meier method, and a comparison of the two groups will be performed via the log-rank test. The influencing factors will be analyzed by univariate and multivariate Cox proportional hazards regression. Statistical significance is set at *P*<.05. The survival prediction model will be established by multivariate Cox regression models and the Kaplan-Meier survival curves. The predictive ability of the final model will be evaluated using the Harrell concordance index (C-index) and calibration curves.

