## Methods

### Study Design

This study is a prospective cohort study. We will compare the treatment outcomes of surgical and nonsurgical methods for SMLC in a real-world clinical scenario. The study will enroll 240 patients (120 patients in the surgical group and 120 patients in the nonsurgical group) from June 1, 2022, to June 30, 2027. The patients will be visited postoperatively at 3, 6, 12, and 24 months. The study is due to be completed on June 30, 2029.

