### Sample Size and Study Timeline

In this study, we plan to compare the overall survival (OS) time between the two groups and explore its prognostic factors. The sample size calculation was based on the survival time and estimation of influencing factors. According to an unpublished retrospective study performed at our center and previous literature [20,21], the average OS time was 11 (SD 4) months in the surgical group and 9 (SD 3) months in the nonsurgical group. Assuming an overall Type 1 error (α) of .05 and Type II error (β) of .1, we need 66 patients in each group. Additionally, there are 12 predictive factors we plan to analyze in the prediction model. According to the sample size estimation method for multivariable regression models, 100 cases in each group are needed (the ratio of surgical to nonsurgical group is 1:1). Considering a final follow-up rate of 80%, a minimum of 120 patients will be required for each group. There were approximately 25 patients undergoing surgery per year at our center; therefore, we plan to enroll the patients over the next 5 years. Since more patients are treated nonsurgically than surgically, all nonsurgical patients treated during the first 5 years will be enrolled.

The study duration is estimated to be 7 years to ensure that all recruited patients are followed up for 2 years. Each visit’s timeline and tasks are presented in Multimedia Appendix 1.

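### The pooled-variance Student t test is named for comparisons whose group sizes are likely to be unequal at some visits; Welch's test would hold the 5% level at very little cost

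*Protocol article*

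**What the plan says.** The Statistical Analysis section gives one test for continuous data, "The 1-tailed unpaired Student" t test, with one threshold ("Statistical significance is set at" *P*<.05). It does not mention unequal variances. Overall survival (OS) and progression-free survival are compared by log-rank, and prognostic factors by Cox regression. The t test is therefore left for baseline variables and for continuous secondary outcomes such as VAS, KPS and SF-36. According to the Secondary Outcomes section, these are assessed at each visit.

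The stated sizes are equal. Study Design says "The study will enroll 240 patients (120 patients in the surgical group and 120 patients in the nonsurgical group", and Sample Size and Study Timeline says "the ratio of surgical to nonsurgical group is 1:1". The latter section also says: "Since more patients are treated nonsurgically than surgically, all nonsurgical patients treated during the first 5 years will be enrolled". Its survival inputs are that "the average OS time was 11 (SD 4) months in the surgical group and 9 (SD 3) months in the nonsurgical group". Visits are at 3, 6, 12 and 24 months.

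**The concern.** The pooled t test estimates one common variance. When sizes and variances both differ, its standard error is wrong. It is too small, and the test too liberal, if the smaller group is the more variable. It is too large, and the test too conservative, if the larger group is. Unequal sizes alone do no harm, and neither do unequal variances at equal sizes.

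Unequal sizes can arise in two ways here. First, the rule to enrol every nonsurgical patient, read literally, gives a larger nonsurgical group. Second, the plan expects shorter survival without surgery, so fewer nonsurgical patients remain to be measured at later visits. Equal variances cannot be taken for granted either. Under the Treatment section, surgery is decided by severe pain, neurological decline or instability, so the groups are selected on symptoms that are also outcomes.

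At stake are the P values and confidence intervals of the continuous secondary comparisons. A reader could not tell in advance in which direction they are off.

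**Working it through.** **1. The plan's own figure.** Inputs from Sample Size and Study Timeline: means 11 and 9, SDs 4 and 3, α .05, β .1, 1:1.

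n per group = (1.960 + 1.282)² × (4² + 3²) / 2² = 10.507 × 25 / 4 = 65.7, so 66.

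This matches "we need 66 patients in each group". It is a two-sided, equal-size calculation (the one-sided version gives 54). It concerns OS, which the t test does not analyse, so these SDs are not SDs of the outcomes at issue.

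**2. Numbers alive at each visit.** Taking the OS inputs as normal, the number alive at t is n × P(OS > t).

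- 3 months: 120 × P(Z > −2) = 117 in each group.
- 6 months: 120 × P(Z > −1.25) = 107 surgical; 120 × P(Z > −1) = 101 nonsurgical.
- 12 months: 120 × P(Z > 0.25) = 48 surgical; 120 × P(Z > 1) = 19 nonsurgical.
- 24 months: about 0 in each group.

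If 240 nonsurgical patients were enrolled (an assumption; the plan gives no number), 240 × P(Z > 1) = 38 would be alive at 12 months.

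**3. Error of the pooled test.** With n₁, σ₁ surgical and n₂, σ₂ nonsurgical:

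- pooled variance s² = [(n₁−1)σ₁² + (n₂−1)σ₂²] / (n₁+n₂−2)
- R = √[s²(1/n₁ + 1/n₂)] / √[σ₁²/n₁ + σ₂²/n₂]
- one-sided error ≈ P(Z > 1.645 R)

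At n₁ = n₂, R = 1 whatever the SDs.

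Example, 120 v 240 with SD ratio 3:2: s² = (119×9 + 239×4)/358 = 5.662. The pooled SE is √(5.662 × 0.0125) = 0.266 and the true SE is √(9/120 + 4/240) = 0.303. R = 0.879, and P(Z > 1.445) = 7.4%.

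Example, 48 v 19 with SD ratio 2:3: s² = (47×4 + 18×9)/65 = 5.385. The pooled SE is 0.629 and the true SE is √(4/48 + 9/19) = 0.746. R = 0.843, and P(Z > 1.386) = 8.3%.

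One-sided error of the pooled test at nominal 5%, by SD ratio (surgical:nonsurgical, all assumed):

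| Sizes (surgical v nonsurgical) | 2:3 | 3:4 | 1:1 | 4:3 | 3:2 |
|---|---|---|---|---|---|
| 120 v 120 (stated) | 5.0% | 5.0% | 5.0% | 5.0% | 5.0% |
| 117 v 117 (3 months, 1:1) | 5.0% | 5.0% | 5.0% | 5.0% | 5.0% |
| 107 v 101 (6 months, 1:1) | 5.2% | 5.1% | 5.0% | 4.9% | 4.8% |
| 120 v 240 (assumed enrolment) | 3.1% | 3.5% | 5.0% | 6.7% | 7.4% |
| 48 v 19 (12 months, 1:1) | 8.3% | 7.3% | 5.0% | 3.1% | 2.6% |
| 48 v 38 (12 months, both imbalances) | 5.8% | 5.6% | 5.0% | 4.5% | 4.3% |

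Simulations of normal data with no true difference agree to about 0.1 percentage point. In the same settings Welch's test stays between 4.9% and 5.2%.

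**4. Two-sided.** A two-sided test does not remove the effect: 2 × P(Z > 1.960 × 0.879) = 8.5% in the first example and 2 × P(Z > 1.960 × 0.843) = 9.9% in the second.

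**The case against.** The strongest reply is that every size the protocol states is equal, and at 120:120, or at 96:96 after 80% follow-up, the Student test holds 5%. That stands. A reader might infer that the plan's own enrolment figures make the groups unequal, and they do not. The imbalance at enrolment comes from one sentence that conflicts with the 1:1 statements and gives no ratio. The Treatment section also limits the nonsurgical group to patients who have both radiotherapy and antitumor drugs, so the ratio is further unknown.

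No SD is given for VAS, KPS or SF-36. Selection by symptoms makes unequal variances plausible, but it does not show which group is more variable or by how much. That also stands, and is why a range is given in both directions.

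The largest drift belongs to a single visit, and the two sources of imbalance partly cancel there (48 v 38). The normal survival model is rough, since it leaves nobody alive at 24 months. At 12 months, comparing outcomes among survivors only is a larger difficulty, and Welch's test does not solve it.

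Finally, a journal article may leave the handling of unequal variances to a fuller plan. This carries less weight, because the article names a specific test that in its usual meaning pools the variances. The point concerns that stated choice, not missing detail.

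**Conclusion.** The point holds as a cheap improvement, not as a demonstrated error. Following the plan is likely to give unequal group sizes for some secondary comparisons, and the named test is then protected only if variances are equal. Over the assumed SD ratios the one-sided error lies between about 2.6% and 8.3% in the worst setting (48 v 19), and between 3.1% and 7.4% at an assumed 120 v 240. It is essentially 5% at the stated sizes and at the 3- and 6-month visits under 1:1.

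A reader might infer that the trial's error rate is generally well off 5%. The documents do not support that. The drift needs unequal sizes and unequal variances together, the SD ratios and the 240 are assumptions, and 48 v 19 rests on treating OS as normal. The primary OS comparison and the Cox models do not use the t test.

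**What to change.** In the Statistical Analysis section, replace the Student t test with Welch's unequal-variance t test, reported with its confidence interval, for all continuous between-group comparisons. If a baseline-adjusted model is used instead, give it heteroscedasticity-robust standard errors. The change is independent of whether the test is one- or two-sided.

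It needs no extra data and only a change of wording. The cost is a small loss of power when variances are in fact equal: none at 120:120, about 0.1 percentage point at 120:240, and about 1 point at 48:19.

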### Treatment

A surgical decision is made following the advice of our institutional multidisciplinary treatment team for spinal metastasis. There are 3 indications for surgery at our center: severe yet drug-resistant local pain, progressive neurological dysfunction, and emerging or latent spinal instability. Otherwise, patients are referred for nonsurgical treatment.

In the surgical group, patients are given surgical treatment, neurological rehabilitation, and adjuvant therapies (ie, SBRT and antitumor drugs). In this setting, we have established a synchronized workflow for surgery-based multimodality therapy instead of the conventional step-by-step schedule. A synchronized workflow means that neurological rehabilitation is incorporated and commenced right before the surgery and that SBRT and antitumor drugs are started early and simultaneously during the process of rehabilitation.

In the nonsurgical treatment group, patients are treated with adjuvant therapies exclusively, including radiotherapy, chemotherapy, targeted therapy, immunological therapy, etc. Considering the existence of various adjuvant modalities, this study will only enroll patients who receive both locoregional radiotherapy and antitumor drugs.

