### Outcomes

#### Primary Outcome

The primary outcome metric of the study is the OS period. OS is defined as the time after the start of any antitumor therapy for SMLC to death of any cause.

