### Previous Studies

Fundamentally, the primary goals of surgery are to restore spinal stability, relieve pain, and decompress tumor mass squeezing of the spinal cord, if any. Yao et al [20] reviewed studies on spinal metastasis and found that surgery could significantly improve neurological function and quality of life, even for patients with advanced lung cancer. However, we have not yet gained firm evidence on the impact of surgery on patients’ survival, though many papers have reported favorable postoperation outcomes. Truong et al [17] recruited patients with SMLC undergoing surgery and found that 14 (16%) out of 87 patients survived beyond 12 months. Chen et al [23] reported the median survival of their cohort to be 12 months; patients undergoing excisional surgery had a longer survival time than those with palliative surgery. Contrarily, in a systematic review by Armstrong et al [21], the authors reported unfavorable outcomes for surgical intervention, of which a shorter median OS was found in the surgical group compared to the nonsurgical group (7.5 months vs 8.5 months). This result was echoed in Amelot et al’s [24] study. These authors concluded that survival of SMLC depends merely on genotype and neurological and personal status, and scarcely on surgical resection. In the past decade, the combination of separation surgery and high-dose hypofractionated SBRT has emerged as an effective option for spinal metastasis, including SMLC [18]. The core principle of this procedure is to circumferentially remove the tumor mass encasing the spinal cord and create a safe zone between the cord and the tumor (≥3mm) for the subsequent delivery of radiation treatment [9,25,26].

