### Strengths and Limitations

The main strength of our study is that it is the first research project to examine the feasibility and outcomes of synchronized adjuvant therapies after surgical intervention for SMLC in a prospective cohort and using a more scientific methodology. This methodological merit will strongly empower the justification for using positive yet invasive treatment modalities instead of conventional palliative care in patients with SMLC. Second, for the purpose of rapid recovery, we are starting rehabilitative intervention at an early stage after surgery. In addition, we recognize the importance of starting adjuvant therapies early after surgery, and this practice will be implemented and examined in our clinical trial.

There are some potential biases in this study that might compromise the reliability and accuracy of the results, but we have designed some solutions to reduce bias. First, though it is difficult to blind the intervention providers and patients, outcome assessors and data processors will be blinded. Second, during the follow-ups, we will encourage face-to-face interviews, but online interviews will also be accepted, considering the possible emergence of scenarios like a COVID-19 surge, in order to reduce the rate of dropout.

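### Surgery follows clinical indications, yet the only stated comparison of the two groups on survival is an unadjusted log-rank test, and no adjusted estimate is designated as the treatment comparison

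*Protocol article*

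**What the plan says.** The Study Design section describes a prospective cohort: "We will compare the treatment outcomes of surgical and nonsurgical methods for SMLC in a real-world clinical scenario". Under Primary Outcome, "The primary outcome metric of the study is the OS period", and the Objective section makes the comparison of treatment outcomes the primary aim.

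The Treatment section states how the groups arise: "There are 3 indications for surgery at our center: severe yet drug-resistant local pain, progressive neurological dysfunction, and emerging or latent spinal instability". It continues: "Otherwise, patients are referred for nonsurgical treatment". It also restricts enrolment to patients who receive both radiotherapy and antitumor drugs.

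For survival, the Statistical Analysis section plots Kaplan-Meier curves and says "a comparison of the two groups will be performed via the log-rank test". It then says "The influencing factors will be analyzed by univariate and multivariate Cox proportional hazards regression", and bases the prediction model on multivariable Cox regression. The Objective section gives treatment modality and neurological function before and after surgery as examples of the prognostic factors to be studied. Exposure Measures adds operation time, blood loss and postoperative stay.

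Strengths and Limitations acknowledges possible biases and says "we have designed some solutions to reduce bias". The solutions given are blinding of outcome assessors and data processors, and online interviews to limit dropout.

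**The concern.** The rule that sends patients to surgery uses features that may themselves affect survival. The document treats neurological function as a prognostic factor (Objective). It also reports a cited study's conclusion that "survival of SMLC depends merely on genotype and neurological and personal status, and scarcely on surgical resection" (Previous Studies). If the groups differ at baseline on such features, an unadjusted log-rank test compares the effect of surgery mixed with case mix.

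The article is not silent on the method. It names the test for the two-group comparison, and that test does not suit groups formed by indication. Neither listed bias solution addresses confounding. At stake is the answer to the primary aim: an imbalance could produce an apparent effect where there is none, or hide a real one.

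**Working it through.** **1. The plan's own sample size.** Inputs from Sample Size and Study Timeline: mean survival 11 (SD 4) versus 9 (SD 3) months, α = 0.05, β = 0.1.

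- Averaged variance: (4² + 3²)/2 = 12.5.
- Two-sided: n = 2 × (1.960 + 1.282)² × 12.5 / 2² = 2 × 10.51 × 12.5 / 4 = 65.7, so 66 per group, as stated. (One-sided gives 54.)

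The survival comparison is thus also sized as an unadjusted two-group contrast.

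**2. What each stated analysis delivers.**

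- Log-rank test: compares the two groups, with no adjustment named.
- Multivariable Cox model: adjusts, but is assigned to influencing factors and prediction. No covariate set is fixed for the surgery effect. Its candidates include measurements taken after treatment (postoperative neurological function) and variables that nonsurgical patients cannot have (operation time, blood loss). Conditioning on these would not estimate the effect of surgery.
- Blinding and online interviews: address assessment bias and dropout, not baseline differences.

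**3. How much an imbalance could matter.** The documents give neither the imbalance nor the prognostic strength, so both are assumed over a range. The simulation used 100 per group, exponential survival with a median of 9 months without the factor, censoring at 24 months, one binary adverse factor, no true effect of surgery and 4,000 runs. Simulation error near 5% is √(0.05 × 0.95/4000) = 0.3 percentage points. Cells show the two-sided rejection rate of the unadjusted log-rank test at nominal 5%, with the apparent hazard ratio (HR) for surgery in brackets.

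| Factor present, surgical vs nonsurgical | Factor HR 1.25 | Factor HR 1.5 | Factor HR 2.0 |
|---|---|---|---|
| 50% vs 50% | 5% (1.00) | 5% (1.00) | 5% (1.00) |
| 60% vs 40% | 6% (1.05) | 8% (1.08) | 15% (1.15) |
| 70% vs 30% | 9% (1.09) | 20% (1.18) | 41% (1.30) |
| 90% vs 10% | 23% (1.20) | 57% (1.39) | 96% (1.75) |

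The log-rank test stratified on the factor rejected in 4.5% to 5.7% of runs, with an HR of about 1.00 throughout. The table puts the adverse factor more often in the surgical group; an imbalance the other way would favour surgery.

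**4. Masking of a real effect.** Assume a true HR of 9/11 = 0.82 and a factor HR of 1.5. At 70% versus 30% the unadjusted HR moves to about 0.97, and stratification returns 0.82.

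**5. The price of adjustment.** In the same setting, the stratified test rejects in 26% of runs at 50% versus 50%, 22% at 70% versus 30%, and 12% at 90% versus 10%. Adjustment removes the bias from a measured factor, but precision falls sharply as overlap shrinks.

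**The case against.** The strongest reply is that an adjusted treatment coefficient may already be planned. Treatment modality is among the prognostic factors in the Objective section. The abstract names Cox regression for overall survival and does not mention the log-rank test, and no sentence calls the log-rank P value primary. Detailed covariate lists are commonly left to a fuller document. This stands in part: a reader might infer that the plan contains no adjustment or excludes treatment from the Cox model, and the text does not support that. What remains is that the only analysis the article assigns to comparing the two groups is the unadjusted test.

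The plan also has one design control. Enrolling only patients who receive both radiotherapy and antitumor drugs aligns part of the co-treatment. It does not balance the features that led to surgery.

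Three further inferences go beyond the documents:

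- That the groups differ by rule on cord compression and performance status. Neither is among the three indications. Of the indications, only neurological status is tied to survival in the text.
- That the bias is large or favours surgery. The indications could worsen prognosis in the surgical group, while choosing fitter patients for surgery could act the other way. In the mildest unbalanced case above the false-positive rate is only 6%.
- That the survival gap quoted with and without an EGFR inhibitor measures the bias. EGFR status is not a surgical indication, and the documents show no imbalance in it between the groups.

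Finally, if nearly every patient with an indication has surgery, adjustment may have little overlap to work with. That limits any fix; it does not rescue the unadjusted test.

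**Conclusion.** The point holds in this form: groups are formed by clinical indication, the only stated comparison of them on overall and progression-free survival is unadjusted, and the planned multivariable model is not designated, or suitably specified, as the treatment comparison. Followed as written, the plan can give a biased answer to its primary aim.

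The size and net direction cannot be derived from the documents. With one assumed factor of HR 1.5 and no true effect, the false-positive rate is about 8%, 20% and 57% at imbalances of 60% versus 40%, 70% versus 30% and 90% versus 10%, against about 5% when stratified. These figures rest on exponential survival and a single binary factor, and show what is possible, not what will occur. If the factor is balanced, there is no inflation. Because the primary comparison is affected and most of the data for adjustment are already collected, this should be corrected before analysis.

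**What to change.** Designate as the primary overall survival comparison the hazard ratio for surgery from a Cox model, or from overlap or propensity weighting, with a covariate set fixed in advance and limited to pre-treatment variables:

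- age, KPS/ECOG, ASIA, VAS, ambulatory status, degree of epidural compression, pathology, gene status and metastatic status, all listed in Exposure Measures;
- the presence of each of the three surgical indications. Spinal instability needs a new field, because Exposure Measures lists no measure of it.

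Exclude postoperative and operation-only variables from this model. Keep the Kaplan-Meier curves and log-rank test as descriptive.

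Record the indications at the multidisciplinary decision. For patients enrolled since June 2022 they may have to be taken from records. Report covariate overlap between the groups. Give an estimate among patients with at least one indication only if enough nonsurgical patients have one. Word the conclusion as an adjusted association for the surgery-based package, with possible residual confounding.

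Cost: a change to the analysis text, a small addition to baseline data, some record review, and a wider interval, possibly much wider where overlap is poor. The list makes 9 + 3 = 12 items besides treatment, the same count as the 12 predictors in the sample size section, though multi-category items use more parameters. No patient's treatment changes.
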